## 6.3 Other assessments

### 6.3.1 Previous and intercurrent illnesses

Illnesses already known at the time of informed consent are to be documented in the eCRF as medical history. Illnesses detected during the clinical trial are to be documented as AEs (see section 7).

### 6.3.2 Previous and intercurrent medical treatments

All medical treatments except for the investigational medical products received by the participant at the beginning, or during the clinical trial, or both, are to be documented in the eCRF as concomitant medication.

#### Special situation:

In the event of a necessary intensive medical treatment (i.e. child in intensive care unit), all medications administered specifically for the treatment of asthma must be documented. For all other medications such as antibiotics, sedatives/anesthetics, nutritional therapeutics, topical medications (e.g. eye, ear, inhalation) and homeopathy, no information on date, dosage and route need to be provided.

### 6.3.3 Laboratory parameters and vital signs

All Laboratory parameters and vital signs are to be documented in the eCRF. The following parameters will be analyzed in this trial:

- Differential blood count
- Glutamate-Pyruvate-Transaminase (GPT)
- Glutamate-Oxalate-Transaminase (GOT)
- Alkaline Phosphatase (AP)
- Urea
- Creatinine
- Total IgE
- Rast (10 Allergens)

Topical (percutaneous) analgesia to reduce pain associated with venipuncture, e.g. amethocaine gel or EMLA cream (Eutectic Mixture of Local Anesthetics), must be applied (may only be omitted in patients who explicitly refuse it). A maximum of 3 puncture attempts to obtain blood (approx. 5 mL) will be performed.

Additionally, we perform next generation sequencing (NGS), enabling analysis of microRNA (miRNA) expression at V1 only (2.5 mL blood).

## 6.4 Epigenetic regulation

In the last decade, the epigenetic regulation of genes has increasingly become the focus of science. Besides histone modification and DNA methylation, non-coding micro ribonucleic acids (miRNAs) are part of the epigenome and regulate a large number of genes post-transcriptionally through interaction with messenger ribonucleic acids (mRNAs). In this way, miRNAs play a

central role in the control of several cellular processes such as cell proliferation, cell differentiation and apoptosis. Dysregulated miRNA expression has been identified in several diseases and is also associated with the pathogenesis of asthma and a number of other lung diseases.

Numerous studies have investigated post-transcriptional regulation in allergy and asthma, but almost no data are available for the particularly vulnerable age of 1-5 years for asthmatics.

#### 6.4.1 miRNAs in Asthma

miRNA-146a plays a central role in the pathogenesis of asthmatic inflammation. Its expression is induced by TNF- $\alpha$  and suppressed by glucocorticoids. miRNA expression profiles of adult asthmatics showed that an increase in miR-146a in plasma was associated with the presence of other reverse markers such as increased blood eosinophil counts, higher asthma control test (ACT) scores and the need for higher doses of ICS. However, inoculation of miR-146a into A549 cells treated with TNF- $\alpha$  +/- glucocorticoids produced an anti-inflammatory effect and increased the efficacy of glucocorticoids by suppressing the TNF- $\alpha$  and IL-6 pathway (65). In addition, their potential role as inflammatory markers in atopic dermatitis has been highlighted (41).

In addition to miRNA-146a, miRNA-21 is increased in expression in childhood asthma and plays a role in eosinophilic asthmatic inflammation (67). Its expression is stimulated by IL-13 (67). MiR-21 induces polarization of naïve T cells towards the Th2 lineage and the synthesis of pro-inflammatory cytokines. Wu et al. reported that miR-21 expression was significantly upregulated in bronchial epidermal cells from asthma patients regardless of treatment (68). There is also a linear relationship between plasma miR-21 and miR-146a expression and FEV1 in pediatric cohorts (69).

Thus, miRNA-146a and -21 seem to be ideal surrogate markers for atopic march. Taken together, NGS is expected to demonstrate dysregulation of miRNA-146a and -21 in preschool asthma compared to healthy controls.

In 2017, British authors published miRNA studies from the CAMP cohort, in which they described eight significantly dysregulated miRNA in childhood asthma that correlated with the threshold of irritation in the MCT. These were: hsa-miR-138-5p, hsa-miR-16-5p, hsa-miR-30d-5p, hsa-miR-203a-3p, hsa-miR-128-3p, hsa-miR-638 (70). The strongest significance was found for miR-296, whose target is IKBKE, among others (70). Targeting IKBKE attenuates airway responsiveness and inflammation in a murine asthma model. Furthermore, IKBKE is a well-described target of the NF $\kappa$ B- gene (71). The impact of the NF $\kappa$ B pathway on asthma and inflammation includes modulation of BHR in mice with allergen challenge (72). Furthermore, IKBKE itself is a known therapeutic target for asthma, whereby targeting IKBKE has been shown to significantly attenuate airway responsiveness and inflammation in a mouse model of asthma (73). Therefore, miR-296 could attenuate the immune response and modulate AHR via the NF $\kappa$ B pathway. Moreover, miR-16-5p was significantly associated with BHR, whose aberrant expression in asthmatic airway cells and its modulatory effect on numerous genes have been described (74).

Based on current research, miRNA profiles represent a highly interesting target to investigate treatment response in preschool asthma. MiRNA profiles provide the potential to serve as easily obtainable biomarkers.

The following objectives are being investigated:

1. To investigate the miRNA profile in children with preschool asthma compared to healthy children
2. To identify a specific miRNA profile characterizing subgroups of preschool asthma

## 7 SAFETY

Safety of the study will be ensured by monitoring of symptom score and rescue medication and lung function. Salbutamol pressurized metered dose inhalers (pMDI) via a spacer as needed will be permitted as rescue medication after visit 1 during observation and after randomization throughout the study.

An asthma exacerbation is defined as an increase of rescue medication (RABA) of more than 6 puffs per day compared to baseline and the use of systemic glucocorticosteroids.

Parents are advised to give in case of a severe asthma exacerbation systemic glucocorticosteroids (Celestamine for 3 days according to manufacture; see table 4 Appendix 15.2) by oral route and contact the investigator within 24 hours.

### 7.1 Definitions

#### 7.1.1 Adverse event (AE)

According to GCP, an AE is defined as any untoward medical occurrence in a patient or clinical investigation patient administered a pharmaceutical product and which does not necessarily have a causal relationship with this treatment. An AE can therefore be any unfavorable and unintended sign (including an abnormal laboratory finding), symptom, or disease temporally associated with the use of a medicinal (investigational) product, whether or not related to the medicinal (investigational) product.

An AE may be:

- a new symptom or a new disease/diagnosis
- an accident
- a change in laboratory parameters
- worsening of a previous medical condition/disease
- recurrence of a disease
- an increase in frequency or intensity of episodic diseases.

Surgical procedures themselves are not AEs; they are therapeutic measures for conditions that require surgery. The condition for which the surgery is required may be an AE. Planned (elective) surgical measures permitted by the clinical trial protocol and the condition(s) leading to these measures are not AEs if the condition leading to the measure was present before inclusion in the trial. In the latter case, the condition should be reported as medical history.

Change in laboratory parameters: The criteria for determining whether an abnormal test finding should be reported as an adverse event are as follows.

The test result:

- is associated with accompanying symptoms, and/or
- requires additional diagnostic testing, and/or
- leads to an unscheduled change in trial dosing, or discontinuation from the trial, and/or a medical/surgical intervention
- is considered to be medically relevant by the investigator or sponsor.

#### 7.1.2 Serious adverse event (SAE)

A SAE is any untoward medical occurrence that at any dose

- results in death,
- is life-threatening,
- requires patient hospitalization or prolongation of existing hospitalization,
- results in persistent or significant disability/incapacity or
- is a congenital anomaly/birth defect or
- is an important medical event.

Death is an outcome of an event. The event that resulted in death should be recorded and reported as SAE.

Life-threatening means that the patient was at immediate risk of death at the time of the SAE; it does not refer to a SAE that hypothetically might have caused death if it were more severe.

If the admission is pre-planned (i.e., elective or scheduled surgery arranged before the start of the trial) or not associated with an AE (e.g., social hospitalization for purpose) or results in a hospital stay less than 12 hours, the serious criterion “hospitalization” is not fulfilled. However, it should be noted that invasive treatment during a hospitalization (less than 12 hours) may fulfill the criteria of “medically important” and may be reportable as a SAE dependent on clinical judgment.

An inpatient rehabilitation program per se does not fulfill the seriousness criteria “hospitalization”. In this case, the investigator should evaluate carefully whether the reason for the inpatient rehabilitation program has to be documented as an AE/SAE.

Persistent or significant disability or incapacity means that there is a substantial disruption of a person’s ability to carry out normal life functions. The irreversible injury of an organ function (e.g., paresis, diabetes, cardiac arrhythmia) fulfills this criterion.

Important medical events that may not be immediately life-threatening or result in death or hospitalization but may jeopardize the patient or may require intervention to prevent one of the other outcomes listed in the definition above, should also usually be considered serious. Examples of such events include allergic bronchospasm requiring intensive treatment in an emergency room or at home, blood dyscrasias, convulsions that do not result in patient hospitalization, or the development of drug dependency or drug abuse. A diagnosis of cancer during treatment should also be considered as medically important.

### 7.1.3 Clarification of the difference in meaning between "serious" and "severe":

The terms "serious" and "severe" are not synonymous but are often used interchangeably. The term 'severe' is used to describe the intensity (severity) of a specific event; the event itself, however, may be of relatively minor significance (such as severe headache). This is not the same as "serious", which is based on the existence of one of the above-mentioned seriousness criteria.

### 7.1.4 Suspected unexpected serious adverse reaction (SUSAR)

A SUSAR is every SAE with an at least possible relationship to the IMP which is unexpected.

An unexpected serious adverse reaction is any adverse reaction, the nature or severity of which is not consistent with the applicable reference safety information.

### 7.1.5 Onset and end date of AEs and SAEs

The onset date of the AE is defined as the date when new signs or symptoms or worsening of a pre-existing condition first occur. The onset date of the SAE is defined as the date when at least one of the above-listed criteria for seriousness occurs.

The end date of the AE is defined as the date when the symptoms resolve, or the event is considered stable by the investigator. The end date of the SAE is defined as the time the seriousness criteria are no longer applicable. The end date of the SAE must not be later than the end date of the corresponding AE. AEs and SAEs that are ongoing at the time of death are considered not resolved or resolving.

## 7.2 Assessment of AEs by investigator

Patients must be carefully monitored for AEs by the investigator. The intensity of the AEs and the causal relation to trial medication and/or procedures are to be assessed.

### 7.2.1 Intensity/Severity

The maximum intensity of an AE will be assessed by the investigator as follows:

- Mild: Temporary event which is tolerated well by the patient and does not interfere with normal daily activities.
- Moderate: Event which results in discomfort for the patient and impairs their normal activity.
- Severe: Event which results in substantial impairment of normal activities of patient.

If the event is serious, the severity reported in the AE must be consistent with the severity included in the SAE report.

### 7.2.2 Causal relation to trial medication/procedures

The assessment of the relationship of an AE to the administration of study drug is a clinical decision by the investigator based on all available information at the time of the documentation. Factors to be considered in assessing the relationship of the AE to study drug include:

- The temporal sequence from drug administration: The investigator has to consider if the event occurred before the first intake of study medication or long time after the last intake. Additionally, the length of time from drug exposure to event should be evaluated in the

clinical context of the event.

- Recovery on discontinuation (de-challenge), recurrence on reintroduction (re-challenge): Patient's response after drug discontinuation or after drug re-introduction should be considered in the view of the usual clinical course of the event in question.
- Underlying, concomitant, or intercurrent diseases: Each report should be evaluated in the context of the natural history and course of the disease being treated and any other disease the patient may have.
- Concomitant medication or treatment should be examined to determine whether any of them may be suspected to cause the event in question.

#### **Positive causal relationship:**

An assessment of 'related' implies a reasonable possibility of a causal relationship between the event and the IMP.

- This means that there are facts (evidence) or arguments to suggest a causal relationship, such as:
- A close temporal relationship
- A common drug reaction to the IMP
- No plausible alternative cause

#### **Negative causal relationship:**

An assessment of 'not related' means that there is no reasonable possibility of a causal relationship between the event and the IMP.

This includes for example:

- Another cause of the AE is more plausible
- A temporal sequence cannot be established with the onset of the AE and administration of the study treatment
- A causal relationship is considered biologically implausible.

### **7.3 Period of observation**

In this trial, the period of observation for collection of AEs extends from the time the subject has signed the informed consent document up to the end of trial visit (regular visit 7).

If the investigator detects a serious adverse event in a trial patient after the end of the period of observation, and considers the event related to the trial treatment or study medication, he should document and report the SAE as described in 7.5.

### **7.4 Documentation of AEs and follow-up**

All AEs (whether serious or not) reported by the patient or detected by the investigator will be documented on the appropriate pages of the electronic case report form (eCRF). AEs must also be documented in the patient's medical records.

If the AE is serious (see section 7.1), the investigator must complete, in addition to the "Adverse Event Page", a "Serious Adverse Event Form" at the time the SAE is detected.

Every attempt should be made to describe the AE in terms of a diagnosis. If a clear diagnosis has been made, individual signs and symptoms will not be recorded unless they represent atypical or extreme manifestations of the diagnosis, in which case they should be reported as separate events. If a clear diagnosis cannot be established, each sign and symptom must be recorded individually.

All patients who have AEs, whether considered associated with the use of the investigational products or not, must be monitored until the outcome of the event can be determined, even after the end of the period of observation, but no longer than the individual end of the trial for this patient. The clinical course of the AE will be followed up according to accepted standards of medical practice.

Should the AE result in death, a full pathologist's report should be supplied, if possible.

## **7.5 Immediate reporting of SAEs by investigator**

**SAEs** must be immediately (at latest within 24 hours of the investigator's awareness) reported to:

**IZKS Mainz**  
**Safety Management**  
**University Medical Center Mainz**  
**[contact]**  
**E-mail: [contact]**

The initial SAE report should be as complete as possible including the essential details of patient's identification (patient number), information on the reporter, the serious adverse event (medical term, diagnosis), the trial medication, and the assessment of the causal relationship between the event and the trial medication. The SAE report must be reviewed and signed by the investigator.

The investigator should provide additional information on the clinical course and the outcome of each SAE as soon as possible (follow up report).

The "Serious Adverse Event Form" is provided in the Investigator Site File.

The investigator can contact the monitor, the safety coordinator, or the trial coordinator in case of questions according to documentation or reporting of SAEs.

## **7.6 Safety evaluation and reporting by sponsor**

The sponsor will ensure that all legal reporting requirements are met. According to GCP, the sponsor is responsible for the continuous safety evaluation of the investigational product(s) and the clinical trial.

SUSARs and safety issues as defined by GCP regulation are determined for expedited reporting: The competent authorities and the ethics committees should be notified as soon as possible but not later than 15 calendar days, and 7 calendar days if it was fatal or life-threatening. All

investigators and the members of the data monitoring committee (DMC) will be informed within the same timeframe. The marketing authorization holder of the IMP should be informed too.

Any safety issues requiring a re-evaluation of the benefit-risk relationship of the IMP will also be reported to the competent authorities and the ethics committees as soon as possible but not later than 15 calendar days (GCP regulation § 13, section 4).

Workflow and procedures concerning safety management will be described in a separate document.

During the clinical trial, IZKS Mainz will submit the Development safety update report (DSUR) including a list of all serious adverse reactions to the ethics committee, the competent authority, and the members of the DMC once a year.

## **7.7 Documentation of special situations**

Special situations such as study medication abuse, misuse, overdose, and medication errors including significant dilution and infusion rate errors have to be documented in the subject's CRF and source documents.

Any special situation with the investigational product occurring during the clinical trial must be reported immediately (at latest within 24 hours of the investigator's awareness) using the "Special Situation Report Form" to:

**IZKS Mainz**  
**Safety Management**  
**University Medical Center Mainz**  
**[contact]**  
**E-mail: [contact]**

If the special situation leads to an adverse event, then only this adverse event has to be documented and reported as an AE/SAE.

## **7.8 Emergency procedures**

During and following a patient's participation in the trial, the investigator should ensure that adequate medical care is provided to a patient for any AEs including clinically significant laboratory values.

## 8 STATISTICS

Details of the statistical analysis of the data collected in this trial will be documented in a Statistical analysis plan (SAP) that will be generated by IZKS Mainz and finalized before closing the database and prior to breaking the blind. The SAP is based on the protocol including all amendments. The document may modify the plans outlined in this protocol; however, any major modifications of the primary endpoint definition and/or its analysis will also be reflected in a protocol amendment. Any deviation from the original statistical plan must be described and justified in the final report. The statistical analysis will be conducted using SAS®.

### 8.1 Sample size

Sample size calculations were based on results published by Vrijlandt E et al. (33). In this study, children aged 1–5 were treated with Tiotropium 5 µg vs placebo as add-on to ICS. After 105 days, 29% of the Tiotropium 5µg group had an asthma exacerbation with pneumonia or asthma worsening, whereas 55.9% of the placebo group had an event. For the present study, it can be assumed that most patients treated with ICS + placebo will suffer from one severe exacerbation within one year, therefore a rate of 90% of placebo patients with a severe exacerbation after one year is anticipated. For the Tiotropium group, a rate of 75% is assumed. The estimation of the difference in rates between the placebo and the Tiotropium group is performed conservatively, assuming a smaller difference than observed after 105 days in the study of Vrijlandt E et al (33). The assumed dropout rate of 15% is converted into a group-loss hazard (0.16) and considered in the sample size calculation. With an event rate of 90% in the control group and 75% in the Tiotropium group and a drop-out-rate of 15%, the sample size will amount to 152 patients when applying a two-sided log-rank test with a hazard ratio of 0.60, a significance level of  $\alpha = 0.05$  and a power of 0.8. The power calculation was performed with PROC POWER in SAS® 9.4.

### 8.2 Analysis populations

All patients whose parents/guardians signed informed consent are considered as enrolled.

All randomized patients will be included in the intention-to-treat (ITT) population. This population is the primary analysis population. Within ITT population analyses patients will be assigned to the treatment to which they were randomized.

To be eligible for the per-protocol population, patients must fulfill the following criteria:

- No concomitant treatment with oral antibiotics longer than 14 days or any monoclonal antibody
- Treatment compliance of at least 80%.

The safety population comprises all patients who received at least one dose of trial treatment. In analyses of the safety population patients will be assigned to the treatment which they actually received. The analysis populations will be defined before unblinding of the study.

### 8.3 Efficacy analyses

The primary population for the analyses of efficacy is the ITT population.

## Determination of primary and secondary measures

**The primary efficacy endpoint** is the time to first severe exacerbations defined by hospitalization and/or at least 3 days of systemic steroids or one day of rectal prednisolone (Rectodelt®). Severe exacerbations were chosen as primary outcome because they are patient-important outcomes that have significant consequences for children, caregivers, and the health care system.

**Key secondary endpoint(s) for all patients:** Secondary endpoints for all patients:

- Number of severe exacerbations
- Exacerbation-free survival time defined as the time from randomization until the first severe exacerbation.
- Percentage of patients requiring systemic corticosteroid rescue for asthma during the 52-week treatment period.
- Number of hospitalizations (severe exacerbation).
- Percentage of days and episodes of > 3 days with use of PRN salbutamol rescue medication during 52-week treatment period (non-severe exacerbation).
- Percentage of days without asthma symptoms assessed by TIPP diary App (PACD).
  - A day without asthma symptoms is defined as a day during which the patient experienced no asthma symptoms (daytime and overnight; question 1, 2, 5, 6, did not use rescue medication (salbutamol) (question 3 and 7), and had no asthma exacerbation/worsening requiring systemic corticosteroids, an unscheduled visit to a doctor's office, or hospital (question 11).
- Percentage of night-time awakenings due to asthma symptoms as assessed by the TIPP diary App.
- Health utilization defined as number of physician visits during treatment.
- Number of missed days in daycare.
- Number of asthma-related events defined by use of antibiotics.
- Evaluation of TRACK at V1, at V4 and at end of treatment.
- CGI-C at end of treatment.

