| SECONDARY ENDPOINTS  | 
Key secondary endpoint(s): number of severe exacerbations, number of hospitalizations (severe exacerbation), (severe) exacerbation-free survival time, number of asthma-related events defined by use of antibiotics, percentage of night-time awakenings due to asthma symptoms as assessed by the electronic patients diary/PACD, percentage of days without asthma symptoms assessed by TIPP diary App (PACD), , percentage of days and episodes of > 3 days with use of PRN salbutamol rescue medication, health utilization (number of physician visits), number of missed days in daycare, result of TRACK, CGI-C at end of treatment and potential biomarkers for treatment response:
 
Eosinophils, IgE, specific IgE to common allergens (birch, grass, Dermatophagoides pteronyssinus, Alternaria, Cladosporium, cat, dog, hen's egg, cow's milk and peanut.
 
Assessment of safety:
Safety will be ensured by analysis of symptom scores and rescue medication use by the electronic diary, and adverse events (AEs).
                                                                                                                                                  |
| STATISTICAL ANALYSIS | 
Efficacy:
The comparison between groups will be made by time to first severe exacerbation within 12 months of therapy.
 
Description of the primary efficacy analysis and population:
The time to first severe exacerbation will be analyzed by Cox regression with factor treatment and the covariates age group and center. Analyses will be performed in the intention-to-treat population and repeated in the per-protocol population as sensitivity analyses. Treatment differences will be displayed by hazard ratios and 95% confidence intervals.
 
Safety: For safety analyses, frequencies of patients experiencing at least one adverse event (AE) will be displayed by system organ class and preferred term according to MedDRA terminology.
 
Secondary endpoints:
For secondary analyses, Cox regression for time to event data will be used and negative binomial regression for count of events. Further secondary endpoints will be assessed by chi-square or Fisher's exact test for categorical variables or t-test or Mann-Whitney-U-test for continuous variables.
 
All tests will be conducted on a two-sided significance level of alpha = 0.05.
 |

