## 3.4 Primary endpoint

**The primary efficacy endpoint** is the time to first severe exacerbations defined by hospitalization and/or at least 3 days of systemic steroids or one day of rectal prednisolone (Rectodelt®). Severe exacerbations were chosen as primary outcome because they are patient-important outcomes that have significant consequences for children, caregivers, and the health care system.

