### Secondary endpoints for all patients:

- Number of severe exacerbations
- Exacerbation-free survival time defined as the time from randomization until the first severe exacerbation.
- Percentage of patients requiring systemic corticosteroid rescue for asthma during the 52-week treatment period.
- Number of hospitalizations (severe exacerbation).
- Percentage of days and episodes of  $\geq 3$  days with use of PRN salbutamol rescue medication during 52-week treatment period (non-severe exacerbation).
- Percentage of days without asthma symptoms assessed by TIPP diary App (PACD).
  - A day without asthma symptoms is defined as a day during which the patient experienced no asthma symptoms (daytime and overnight; question 1, 2, 5, 6, did not use rescue medication (salbutamol) (question 3 and 7), and had no asthma exacerbation/worsening requiring systemic corticosteroids, an unscheduled visit to a doctor's office, or hospital (question 11).
- Percentage of night-time awakenings due to asthma symptoms as assessed by the TIPP diary App.
- Health utilization defined as number of physician visits during treatment.
- Number of missed days in daycare.
- Number of asthma-related events defined by use of antibiotics.
- Evaluation of TRACK at V1, at V4 and at end of treatment.
- CGI-C at end of treatment.

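### The endpoint labelled non-severe exacerbation is defined by salbutamol use alone, so it can include severe exacerbations and reflect an effect on them

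*Protocol*

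**What the plan says.** Section 8.3 (Determination of primary and secondary measures) lists among the secondary endpoints "Percentage of days and episodes of > 3 days with use of PRN salbutamol rescue medication during 52-week treatment period (non-severe exacerbation". Sections 3.4 and 6.1 carry the same item with the same label ("use of PRN salbutamol rescue medication during 52-week treatment period (non-severe exacerbation"). The Synopsis lists it without the label: "days with use of PRN salbutamol rescue medication, health utilization (number of physician visits".

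The primary endpoint in section 3.4 is "time to first severe exacerbations defined by hospitalization and/or at least 3 days of systemic steroids or one day of rectal prednisolone (Rectodelt". Section 8.3 repeats the criterion as "hospitalization and/or at least 3 days of systemic steroids or one day of rectal prednisolone". Salbutamol plays no part in it.

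Section 7 describes an asthma exacerbation as an "increase of rescue medication (RABA) of more than 6 puffs per day compared to baseline and the use of systemic glucocorticosteroids". Sections 4.3 and 7 permit salbutamol as needed from visit 1 throughout the study. Section 8.3.2 assigns endpoints of this kind to a t-test or Mann-Whitney test if continuous, or to a chi-square or Fisher test if categorical. It treats p below 0.05 as significant.

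**The concern.** The label names a category that ought to exclude severe exacerbations, but the rule under it does not. A child who takes salbutamol for several days and then needs systemic steroids or admission meets both definitions in a single illness.

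If tiotropium prevented severe events and did nothing to milder ones, the salbutamol episodes attached to the prevented events would disappear too. The endpoint would then move in favour of tiotropium, and under its present label the result would read as a benefit on non-severe exacerbations. That is a misattribution of effect. It does not mean that the salbutamol measure is wrong in itself: as an all-cause measure of rescue use it is ordinary and useful.

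**Working it through.** **Definitions side by side**

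| Category | Criterion | Excludes the other? |
|---|---|---|
| Severe exacerbation (3.4, 6.1, 8.3) | Admission, or systemic steroids for a stated time | No |
| Labelled non-severe (3.4, 6.1, 8.3) | Days, and multi-day episodes, with salbutamol | No |
| Exacerbation (7) | More than 6 extra puffs per day and systemic steroids | Not applicable |

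The first two can both be met. Section 7 makes overlap likely, because it pairs raised rescue use with steroids, but it gives no duration.

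**The plan's own figures.** The protocol gives no figure for this endpoint, so I checked the planning rates in section 8.1 instead.
- Hazards: −ln(1 − 0.90) = 2.303 and −ln(1 − 0.75) = 1.386 per year. Their ratio is 0.602, against the stated 0.60.
- Schoenfeld events at 0.60, two-sided 5%, 80% power: 4(1.960 + 0.842)²/(ln 0.60)² gives 121.
- Event probability with loss hazard g = 0.16, from h/(h+g) × (1 − exp(−(h+g))): 0.855 and 0.706, mean 0.780.
- N = 121/0.780, or 156 rounded up to an even number. This is within 3% of 152.

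**Spurious rate ratio.** Let L be the yearly rate of truly non-severe episodes, equal in both arms, and f the share of severe events that carry a qualifying salbutamol run. Neither is in the protocol. The planning hazards are for a first event and are used here as constant rates of recurrent events, which is a further assumption. Then

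ratio = (L + 1.386f)/(L + 2.303f).

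Example, L = 2 and f = 1: 3.386/4.303 = 0.79.

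| L per year | f = 0.5 | f = 0.75 | f = 1 |
|---|---|---|---|
| 1 | 0.79 | 0.75 | 0.72 |
| 2 | 0.85 | 0.82 | 0.79 |
| 4 | 0.91 | 0.88 | 0.85 |
| 8 | 0.95 | 0.93 | 0.91 |

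At L = 2 and f = 0.75, the share of placebo episodes that belong to severe events is 1.727/3.727 = 46%.

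**Chance of p < 0.05.** I assumed 76 per arm (the allocation ratio is not stated) and mean exposure of 0.923 year. The standard error of the log ratio is √[(1/m₁ + k)/76 + (1/m₂ + k)/76], where m is the expected count per child and k an assumed dispersion. At L = 2, f = 0.75, k = 0.5, m is 2.81 and 3.44, the standard error is 0.147 and |ln 0.816| is 0.204. The chance is about 28%; a simulated Mann-Whitney test gives 25%. Over L = 1 to 8, f = 0.5 to 1 and k = 0 to 1 the approximation runs from 6% to 89%. With severe-linked episodes removed, the simulated test rejects in 4.4% to 5.1% of runs.

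**Exclusion under a different mechanism.** If tiotropium converts severe episodes into milder ones, the all-episode count is equal in the two arms. The count after exclusion rises on tiotropium: [2 + 0.75 × (2.303 − 1.386)]/2 = 1.34 at L = 2, f = 0.75.

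**The case against.** The strongest reply is that the bracket is itself the restriction. Severe exacerbation is a defined term, so a non-severe one is whatever fails that definition, and only the linking rule is left to the SAP, which is not at hand. The neighbouring item "Number of hospitalizations (severe exacerbation" could be read as a filter in the same way.

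That reading is possible but not the natural one. The bracket closes an item that also covers the percentage of all salbutamol days. The next item, on symptom-free days, spells out its steroid and hospital conditions, so the authors wrote conditions down where they meant them. The Synopsis drops the label altogether. Even as a filter, the bracket gives no way to attribute an episode. A SAP may add a rule, but the protocol's rule and label would still disagree.

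Other parts of the reply stand:
- A reader might infer that a severe exacerbation will usually meet the salbutamol rule. Section 7 gives an intensity and no duration, and the diary asks what the caregiver gave, so inpatient doses may not be recorded. The overlap share is unknown.
- A reader might infer that the endpoint exists to show a benefit on milder disease. The protocol does not say so; the secondary objective in 2.2 is health utilization.
- Sharing events with the primary endpoint is normal in this list and no fault in itself. The fault is the label.
- Exclusion selects on an event that treatment may affect, so it cannot stand alone as the remedy.

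**Conclusion.** The point holds as a conflict between label and rule in sections 3.4, 6.1 and 8.3. The severe and non-severe categories are not mutually exclusive, and a reduction in severe events alone could appear as a benefit on non-severe ones. This needs some overlap between the categories and a real effect on severe events.

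The size cannot be determined from the protocol. The range of about 0.72 to 0.95 depends on the assumed background rate and overlap, and on reading first-event hazards as recurrent rates. The rejection rates also depend on the assumed dispersion and equal arms, and they describe a null hypothesis about truly non-severe episodes that the protocol never states. One might conclude that the trial carries a particular inflated error rate here; the documents do not support any single figure. A false significant result is possible, not certain.

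The primary endpoint and the sample size of 152 are unaffected. The correction concerns one secondary endpoint and is worth making before unblinding.

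**What to change.** 1. Report the percentage of salbutamol days and all multi-day salbutamol episodes as an all-cause rescue-use endpoint, without the non-severe label.
2. If a non-severe exacerbation endpoint is wanted, count only qualifying episodes that do not overlap a severe exacerbation. Fix the linking window before unblinding; 7 days either side is one example and has no basis in the documents. Present this count together with the all-episode count and the severe/non-severe split, so that conversion of severe into milder episodes can be seen.
3. Use one wording in 3.4, 6.1, 8.3 and the Synopsis. The episode threshold needs reconciling in the same edit: it is more than 3 days in the Synopsis and 8.3, and at least 3 days in 3.4 and 6.1. That mismatch is a separate matter.

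The cost is the wording change and one extra derivation. The diary in Appendix 15.5 already records β-agonist use (questions 2, 3, 9 and 10) and admissions and systemic steroids (question 8). The non-severe count will have fewer episodes and slightly less precision, and diary-based counts are limited to the months when the diary is kept, since it pauses from May to August.
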